# Protocol Summary

| applicant | Nanfang Hospital, Southern Medical University |
| --- | --- |
| phase | Ⅳ |
| indication | Patients with hematological malignancy who are scheduled to receive haploidentical hematopoietic stem cell transplantation (haplo-HSCT) |
| objectives | compare the incidence of viral infections and graft-versus-host disease (GVHD) in patients receiving haplo-HSCT between 7.5 mg and 10.0 mg ATG groups. |
| study design | prospective, multi-center, controlled, open-label, randomized phase Ⅳ study |
| required subject | subjects |
| Study sites | 4 (Nanfang Hospital, Peking University People's Hospital, Fujian Medical University Union Hospital, Xiangya Hospital) |
| Screening Criteria | subjects who are scheduled to receive haplo-HSCT without treatment contraindication |
| Control Group | 10.0 mg/kg ATG (2.5mg/kg/day from days -4 to -1 before transplantation) |
| Experimental Group | 7.5 mg/kg ATG (2.5mg/kg/day from days -3 to -1 before transplantation) |
| Primary Endpoint | Incidence of EBV DNAemia post-transplantation |
| Secondary Endpoints | incidence of grade II to IV and grade III to IV aGVHD within 100 days post-transplantation; hematopoietic engraftment; cGVHD; EBV-associated diseases; CMV infections (CMV DNAemia and associated diseases); relapse; non-relapse mortality (NRM); overall survival (OS); disease-free survival (DFS) and tolerability |
| Study procedures | This is a prospective, multi-center, controlled, open-label, randomized phase Ⅳ study. A total of 412 subjects with acute leukemia who were scheduled to receive haplo-HSCT and met the inclusion criteria is required. After giving written informed consent, all subjects will be randomly assigned to 7.5mg/kg (7.5 mg group) or 10.0mg/kg ATG group (10.0 mg group) in a 1:1 ratio. Viral infections (EBV and CMV), GVHD and survival will be evaluated. |
|  |  |

# 1. Background

Allogeneic hematopoietic stem cell transplantation (allo-HSCT) has been regarded as a curative strategy for acute leukemia. Lack of HLA-matched donor is the obstacle to widespread application of allo-HSCT. A growing body of clinical studies has suggested that haplo-identical related donor HSCT (haplo-HSCT) has comparable outcomes with transplants from matched sibling and unrelated donor, following the improvement of transplant technique in the last few years, such as immunosuppressive conditioning, graft manipulation, infection and graft-versus-host disease (GVHD) management. As a result, haplo-identical related donor is now considered an alternative for allo-HSCT. However, GVHD and infections remain main causes of morbidity and mortality after haplo-HSCT except leukemia relapse.

Now, the strategies of GVHD prophylaxis mainly included ex vivo and in vivo T-cell-depletion (TCD) in haplo-HSCT. Although ex vivo TCD could reduce the morbidity and mortality of GVHD, it also affects immune reconstitution leading to high incidences of infections and disease relapse, and so on, making less benefit for survival. Therefore, ex vivo TCD has been gradually replaced by in vivo TCD. Among the in vivo TCD strategies, two major methods are used: antithymocyteglobulin (ATG)/antilymphocyte globulin (ALG) or post-transplantation cyclophosphamide (PTCy). The ATG strategy has been widely used, especially in China, resulting in a declined infections and relapse compared with ex vivo TCD. Nevertheless, infections, especially viral infections, remain important drawback of ATG strategy. Several studies have demonstrated the risk of infections depends on the dosage of ATG. To data, the optimal dose of ATG which offers sufficient efficacy of GVHD prophylaxis and minimizes risk of infections is unknown in the haplo-identical setting. In our previous single-center study, 6mg/kg rabbit-ATG had a lower incidence of EBV infection, but higher risk of severe acute GVHD (aGVHD) and chronic GVHD (cGVHD) in haplo-HSCT, compared 10 mg/kg rabbit-ATG. Therefore, we design this multicenter randomized study to evaluate the effect of 7.5 mg/kg and 10 mg/kg rabbit-ATG aiming at lowering viral infections without increasing GVHD in haplo-HSCT.

# 2. Objectives

## 2.1 Primary Objective

The primary objective of this study is to compare the incidence of EBV DNAemia post-transplantation in patients receiving haplo-HSCT with 7.5 mg and 10.0 mg ATG for GVHD prophylaxis.

## 2.2 Secondary Objective

The secondary objective of this study is to compare the incidence of aGVHD and cGVHD, EBV-associated diseases, CMV infections (CMV DNAemia and associated diseases), relapse, survival and tolerance in patients receiving haplo-HSCT with 7.5 mg and 10.0 mg ATG for GVHD prophylaxis.

# 3. Study Design

This is a prospective, multi-center, controlled, open-label, randomized (1:1) phase Ⅳ study of comparison of different dosages ATG for GVHD prophylaxis. (7.5 mg/kg vs. 10.0 mg/kg) in patients receiving haplo-HSCT

Screening:

The subjects or their legally acceptable representative will provide written informed consent. EBV and CMV antibody will be performed in all the haplo-HSCT recipients and donors before transplantation. EBV and CMV-DNA was tested in all the recipients and donors.

Treatment:

Based on their assignment, subjects will receive 7.5 mg ATG (2.5mg/kg/day from days -3 to -1 before transplantation) or 10.0 mg ATG (2.5mg/kg/day from days -4 to -1 before transplantation).

# 4. Subject Selection Criteria

## 4.1 Subject Selection Criteria

### 4.1.1 Number of Subjects

A total of 412 subjects will be randomized to 7.5 mg group or 10.0 mg ATG group.

### 4.1.2 Inclusion Criteria

The subjects must meet the following criteria to be eligible for study entry:

1. Signed Informed Consent Form
2. Age≥14 years old and ≤65 years
3. Patients with acute leukemia
4. Ability to comply with study and follow-up procedures

### 4.1.3 Exclusion Criteria

1. Cardiac dysfunction (particularly congestive heart failure, ejection fraction <50%)
2. Respiratory failure ( PaO_2_ ≤60mmHg)
3. Hepatic abnormalities (bilirubin ≥3 mg/dL, aminotransferase >5 times the upper limit of normal)
4. Renal dysfunction (creatinine clearance rate < 30 mL/min)
5. ECOG performance status score 3 to 5
6. Uncontrolled infection
7. A history of anaphylaxis attributed to ATG
8. Subjects who have CMV- and EBV DNAemia or CMV and EBV associated diseases at transplantation
9. Subjects of whom the donor have CMV- and EBV DNAemia at transplantation

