## 4.2. Removal Criteria

Subjects who have participated in the study will be removed from statistical analysis for any of the following:

1. Subjects who are ineligible for this study

2. Deviation(s) from the protocol

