# 5. Study Procedures

## 5.1 Treatment Assignment

Patients who meet the eligibility criteria and consent to participate will be randomized at 1:1 ratio to receive 7.5 mg/kg ATG (7.5 mg group, experimental Group) or 10.0 mg/kg ATG (10.0 mg group, control group).

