## 5.2 Study Treatment

ATG (Thymoglobulin; rabbit anti-human thymocyte immunoglobulin, Imtix Sangstat, Lyon, France) will be administered in 2.5mg/kg/day from days -3 to -1 in 7.5 mg group, and days -4 to -1 in 10.0 mg group. If ATG-related diarrhea or grade III fever (according to the Common Terminology Criteria for Adverse Events, the CTCAE, version3.0) occurred, additional dexamethasone (5.0 mg) would be given for treatment, and the speed of ATG infusion would be slowed down. If the subject experienced severe ATG associated allergic reaction at the first dose, he will be excluded from the study.

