### 9.2.1 Analysis of efficacy

For each numeric variable, the normality of distribution will be preliminarily assessed by the Kolmogorov-Smirnov test. Summary statistics, including proportions, mean, medians, and ranges, were used to describe the patient characteristics, pre-transplantation variables, adverse events, and immune recovery. The χ2 test and Mann-Whitney U test were used for categorical variables and continuous variables, respectively.

Time to acute GVHD, relapse, OS, and DFS were measured from the date of HSCT (d 0). OS and DFS were estimated using the Kaplan-Meier method. Considering the competing risks of death, cumulative incidence curves in a competing risks setting were used to calculate probabilities of aGVHD, cGVHD, viral infections (EBV- and CMV- emia as well as associated diseases) and relapse. The Cox proportional hazards model will be used to evaluate the associations of patient and transplant characteristics with outcomes in multivariate analysis. The risk factors for EBV and CMV infections include age and gender of patients; conditioning; EBV serostatus in patients and donors; CMV serostatus in patients and donors; ATG dose. The risk factors for aGVHD and cGVHD include age and gender of patients; conditioning; HLA disparity; age and gender of donors and ATG dose. The risk factors for survival and relapse include age and gender of patients; disease category; disease status; ATG dose.

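### Exclusion criteria 8 and 9 date viral status to day 0, after randomisation and after ATG, so with Section 4.2 they allow post-randomisation removal on the primary-endpoint virus; their wording also leaves one virus or both unclear

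*Protocol*

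**What the plan says.** Criterion 8 in Protocol Section 4.1.3 excludes "Subjects who have CMV- and EBV DNAemia or CMV and EBV associated diseases at transplantation". Criterion 9 excludes "Subjects of whom the donor have CMV- and EBV DNAemia at transplantation". Section 9.2.1 labels the date of transplantation day 0.

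Section 5.1 puts eligibility before assignment: "Patients who meet the eligibility criteria and consent to participate will be randomized at 1:1 ratio". Section 5.2 gives ATG at "2.5mg/kg/day from days -3 to -1 in 7.5 mg group, and days -4 to -1 in 10.0 mg group".

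Section 4.2 lists, among the reasons for removing a participant from the statistical analysis, "Subjects who are ineligible for this study".

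Under Screening, Section 3 states that "EBV and CMV-DNA was tested in all the recipients and donors". It gives no day for this test, and criteria 8 and 9 do not refer to it.

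The primary endpoint (Section 6.2) is EBV DNAemia within one year of transplantation. Section 6.1 defines EBV viremia as two consecutive positive results.

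**The concern.** Eligibility should be settled from information available before randomisation. Here two criteria are dated to a point when assignment is known (the trial is open-label) and the two groups have received different amounts of ATG. Together with the removal rule, this allows selection after randomisation on a variable closely tied to the primary outcome. For recipients the selection could depend on the arm, since the Background (Section 1) itself says that infection risk depends on ATG dose. The comparison would then no longer be fully protected by randomisation.

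The second difficulty is the word joining the two viruses. If only patients positive for both are excluded, a recipient positive for EBV alone can enter. Once two consecutive positives are recorded, that patient could count as a primary event that the ATG dose did not cause. Such events dilute the difference between arms.

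**Working it through.** **Timeline.** No randomisation day is stated, so the order is inferred from the dosing days.

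- The 10.0 mg group is dosed from day -4 and the 7.5 mg group from day -3 (Section 5.2). Assignment must be known no later than the day -4 dose.
- ATG ends on day -1 in both groups. By then the groups differ by one dosing day, 2.5 mg/kg.
- Criteria 8 and 9 are judged on day 0 (Sections 4.1.3 and 9.2.1).

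Read literally, neither criterion can be settled before randomisation, so Sections 4.1.3 and 5.1 cannot both be followed as written. Section 4.2 then turns a day-0 finding into removal from analysis.

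**The plan's own figure.** Inputs from Section 9.1.1: 30% and 42%, one-sided 5%, power 80%, 1:1, 5% dropout. With unpooled variance,

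n = (1.645 + 0.842)² × (0.30×0.70 + 0.42×0.58) / 0.12² ≈ 194.8, so 195 per group; 195 / 0.95 = 205.3, so 206 per group and 412 in total.

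The stated size is reproduced, and nothing in this point changes it.

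**Size of the effect.** The protocol gives no day-0 positivity rate. All shares below are assumptions.

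(a) *A share q of each arm enters already EBV-positive and all become events.* The arm's rate becomes r(1 - q) + q, a rise of q(1 - r); the difference becomes 12(1 - q) points.

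| q | 7.5 mg group | 10.0 mg group | Difference |
| --- | --- | --- | --- |
| 1% | 30.7% (+0.7) | 42.6% (+0.6) | 11.9 points |
| 5% | 33.5% (+3.5) | 44.9% (+2.9) | 11.4 points |

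With 196 evaluable per group (206 × 0.95 = 195.7), one-sided power (normal approximation, pooled variance under the null) is 79.9% at q = 0 and 74.9% at q = 5%.

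(b) *A share x of each arm is removed, with event rates unchanged.* On top of 5% dropout, x = 5% leaves 195.7 × 0.95 = 185.9 per group. One-sided power goes from 79.8% to 78.0%.

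(c) *Removal depends on the arm.* A share e of the 10.0 mg group is removed, all of whom would have been events, and none of the 7.5 mg group:

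- e = 2%: (0.42 - 0.02) / 0.98 = 40.8%, difference 40.8 - 30.0 = 10.8 points.
- e = 5%: (0.42 - 0.05) / 0.95 = 38.9%, difference 38.9 - 30.0 = 8.9 points.

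The mirror case, 2% removed from the 7.5 mg group only, gives (0.30 - 0.02) / 0.98 = 28.6% and a difference of 13.4 points. If a higher dose raises early positivity, shrinkage is the likelier direction, but the text does not guarantee it.

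**The case against.** The best defence is that the criteria are loosely worded and that a check before randomisation was intended. Section 3 places recipient and donor viral DNA testing under Screening, Section 5.1 randomises only eligible patients, and Section 6.4 starts scheduled monitoring after transplantation. No planned sample between randomisation and day 0 is described that would trigger a removal. This makes the benign reading plausible. It does not remove the problem, because the screening test is undated and the criteria name a different time point.

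It can also be said that the harm comes from the removal rule in Section 4.2, which affects every criterion. That is fair. But most criteria can be judged before assignment; these two, as dated, cannot.

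Four stronger inferences are not supported:

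- *The protocol admits patients positive for EBV alone.* Section 9.2.1 uses the same conjunction to list EBV and CMV infections as separate outcomes, so exclusion for either virus is an equally fair reading. The text is ambiguous.
- *A positive result on day 0 is at once a primary event.* The definition in Section 6.1 needs two consecutive positives, and the endpoint counts DNAemia after transplantation. By the same definition, a single sample on the day could not establish viremia for criterion 8 either.
- *Criterion 9 selects by arm.* ATG given to the recipient cannot change the donor's viral status. That exclusion would also come after randomisation, but it cannot depend on the arm by this route.
- *The trial result is biased.* Nothing shows that any patient was removed or admitted on these grounds, or that one more ATG day changes day-0 positivity.

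**Conclusion.** The timing point stands. As written, criteria 8 and 9 are assessed after randomisation and after all assigned ATG, and Section 4.2 removes those who fail them. For recipients this permits selection on the primary-endpoint virus in an open-label trial. The wording on the two viruses is an unresolved ambiguity rather than an established gap.

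The likely effect is modest. Under assumed shares of 1-5% prevalent positives per arm, the loss is 0.1 to 0.6 of the planned 12 points. Removal confined to the 10.0 mg arm, at an assumed 2-5%, would cost about 1.2 to 3.1 points. These figures rest on assumed rates and on every affected patient being an event. The change should be made because it is cheap and closes an avoidable challenge to the primary comparison; it is not a fatal defect.

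**What to change.** - Apply criteria 8 and 9 to the last recipient and donor EBV and CMV DNA sample before randomisation, and give the window for that sample. Section 3 already lists the test under Screening.
- State whether either virus or both must be present to exclude, separately for DNAemia and for disease, and whether one positive result suffices.
- State that patients who turn positive between randomisation and day 0 stay in the primary analysis in their assigned arm.
- Reconcile Sections 3, 4.1.3, 4.2 and 5.1 accordingly.
- Report how the criteria were applied so far. Section 9.1.1 describes an analysis of the first 210 patients, so a change of wording could alter eligibility partway through unless it only records existing practice.

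The cost is a short amendment, probably with no new testing and no change to the 412. The downside is that a few patients positive on day 0 remain in the analysis and dilute the difference slightly, as in (a) of the working.

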## 4.2. Removal Criteria

Subjects who have participated in the study will be removed from statistical analysis for any of the following:

1. Subjects who are ineligible for this study

2. Deviation(s) from the protocol

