## 6.4 Methods and Schedule Of endpoints assessments

Patients will be followed for adverse events for 30 days after study treatment post-transplantation. The CMV-DNA and EBV-DNA loads of blood will be detected regularly by quantitative real-time polymerase chain reaction (RQ-PCR). The threshold for EBV-DNA and CMV-DNA copies in plasma provided by the manufacturer (ZJ Bio-Tech Co., Ltd., Shanghai, China) is less than 500 copies/ml. EBV-DNA or CMV-DNA is considered positive when the copies exceeded 500 copies/ml. The CMV-DNA and EBV-DNA of blood is monitored weekly for the first 3 months after transplantation; during the 4^th^ to 9^th^ month post-transplantation, the monitoring frequency was once every 2 weeks; and the frequency was once a month for the 10^th^ to 12^th^ month. If positive, viral load will be monitored twice a week. Endpoints assessments will be assessed according to the criteria previously mentioned throughout the study period.

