# 9. Data Analysis and Statistical Considerations

## 9.1 Study Design Considerations

This is a prospective, multi-center, controlled, open-label, randomized (1:1) phase Ⅳ study of comparison of different dosages ATG for GVHD prophylaxis (7.5 mg/kg vs. 10.0 mg/kg) in patients receiving haplo-HSCT. The primary Endpoint was incidence of EBV DNAemia within 1 year post-transplantation, and the study is designed to determine if 7.5 mg/kg ATG is superior to 10.0 mg/kg in the study population with respect to EBV DNAemia.

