### 9.2.2 Analysis of safety

All the patients in the study will be included in the safety analysis. The safety end points included clinical symptoms and laboratory abnormalities, laboratory values and vital signs analyzed by means of the chi-square test.

All P values are based on two-sided hypothesis tests. Alpha is set at 0.05. SPSS 19.0 (SPSS Inc., Chicago, IL, USA) and R version 3.4.3 (R Development Core Team, Vienna, Austria) were used for all data analysis.

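### Section 4.2 drops ineligible patients and patients with any protocol deviation from the analysis after randomisation, and no all-randomised efficacy set protects the EBV DNAemia comparison

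*Protocol*

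**What the plan says.** Section 4.2 of the protocol sets the only rule on who enters the efficacy analysis: "Subjects who have participated in the study will be removed from statistical analysis for any of the following". It gives two reasons, "Subjects who are ineligible for this study" and "Deviation(s) from the protocol". It does not separate major from minor deviations, set a time limit, say who decides, or confine the rule to a secondary analysis. No intention-to-treat or all-randomised efficacy set appears elsewhere in the protocol.

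Three other places bear on the rule:

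- Section 5.2 adds a further exclusion after randomisation: "If the subject experienced severe ATG associated allergic reaction at the first dose, he will be excluded from the study".
- Section 4.1.3 times a virological exclusion criterion at the transplant: "Subjects who have CMV- and EBV DNAemia or CMV and EBV associated diseases at transplantation". Under section 5.2, ATG runs up to day -1, so this status is settled after allocated treatment has begun.
- Section 9.2.2 goes the other way for safety: "All the patients in the study will be included in the safety analysis".

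Section 9.1 describes a "prospective, multi-center, controlled, open-label, randomized (1:1) phase Ⅳ study" designed to show superiority on EBV DNAemia. Section 6.4 adds, for the viral tests that define this endpoint: "If positive, viral load will be monitored twice a week".

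**The concern.** Randomisation protects the comparison only if patients are analysed as randomised. Section 4.2 lets events after randomisation decide who is counted, and a deviation of any size is enough. The trial is open-label and PCR results arrive throughout the first year, so a removal may be decided when both the arm and the primary outcome are known. Nothing in the rule prevents that.

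Two features could tie removal to outcome or arm. EBV-positive patients move to more frequent testing and so have more scheduled procedures to miss. A patient can also become ineligible on virological grounds after ATG has started, and then fall under the first removal reason. What is at stake is the validity of the superiority test and, to a lesser degree, its power.

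**Working it through.** **Inputs.** Section 9.1.1 gives 30% (7.5 mg) and 42% (10.0 mg), one-sided 5%, 80% power, 1:1 allocation, 5% drop-out and 206 per group. Section 6.4 gives the test schedule. All other shares below are assumptions, because the protocol gives no figure for removals.

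**1. The plan's own figure.** With unpooled variance, n = (1.645 + 0.842)² × (0.30×0.70 + 0.42×0.58) / 0.12² = 194.75, so 195 per arm. Then 195/0.95 = 205.3, so 206 per arm and 412 in total. The pooled form gives 197, and 197/0.95 = 207.4, so 208. The stated 412 is reproduced, so the sample size is not the error here.

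**2. Unselective removal.** Power = Φ{[0.12 − 1.645·√(2×0.36×0.64/n)] / √[(0.30×0.70 + 0.42×0.58)/n]}.

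- n = 206 (none removed): 81.6%
- n = 195.7 (5%, the planned loss): 79.8%
- n = 185.4 (10%, assumed): 77.9%
- n = 154.5 (25%, assumed): 71.1%

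There is no bias in this case.

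**3. Selectivity equal in both arms.** The first-year schedule has about 13 weekly + 13 two-weekly + 3 monthly = 29 tests. Assume that each test is missed independently with probability m, that one miss leads to removal, and that EBV-positive patients have 8 extra tests (37 in all). The share kept is (1−m)^29 for negatives and (1−m)^37 for positives. The observed rate is p·k₊ / [p·k₊ + (1−p)·k₋].

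- m = 1%: 25.3% of negatives and 31.1% of positives are removed. The rates read 28.34% and 40.05%, a difference of 11.7 points.
- m = 2%: 44.3% and 52.6% are removed. The rates read 26.72% and 38.12%, a difference of 11.4 points.

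Both rates fall, but the difference moves only slightly from 12.0 points, and towards zero.

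**4. Selectivity in one arm only.** Assume no true difference, with 36% in both arms (the midpoint of 30% and 42%). In the 10.0 mg arm 5% are removed at random, leaving 195.7. In the 7.5 mg arm 5% of negatives and a share q of positives are removed. The observed 7.5 mg rate is a = 0.36(1−q) / [0.36(1−q) + 0.64×0.95]. The chance of a false superiority claim is Φ{[(0.36 − a) − 1.645·SE₀]/SE₁}, where SE₀ is the pooled and SE₁ the unpooled standard error.

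- q = 5%: a = 36.0%, false-claim risk 5.0%.
- q = 10%: a = 0.324/0.932 = 34.8%, 192.0 analysed, (0.0124 − 1.645×0.0486)/0.0486 = −1.39, risk 8.2%.
- q = 20%: a = 0.288/0.896 = 32.1%, 184.6 analysed, (0.0386 − 1.645×0.0486)/0.0486 = −0.85, risk 19.7%.

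The arm would hold 0.36×206 = 74 positives, so q = 10% and 20% mean about 7 and 15 of them removed, against about 4 at the 5% background. At the two-sided 0.05 level of section 9.2.2, the risk in the favourable direction goes from 2.5% to 4.4% and 12.1%.

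**The case against.** A reader might infer that section 4.2 removes EBV-positive patients preferentially, and so favours one dose. The protocol does not support that. It contains no rule or figure to that effect, only features through which it could happen. The testing rule is the same in both arms, and step 3 shows that a mechanism shared by the arms barely changes the difference.

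The 25% and 44% removal shares should not be read as forecasts either. The protocol does not say that one missed PCR is a deviation. Misses clustered within patients would put fewer patients over the line, and patients who die in the first year do not complete 29 tests. The extra ATG day in the 10.0 mg arm is a weak argument: those days precede transplantation, so a dosing deviation there comes before the post-transplant EBV outcome.

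Nor does the protocol say who decides on deviations, so it cannot be claimed that whoever decides knows arm and outcome. Section 12 mentions a monitoring panel blinded to assignment, but gives it no part in removals, so this is no safeguard.

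Finally, section 9.2 refers to a prespecified statistical analysis plan, which might define an all-randomised set. It would then contradict an explicit protocol rule, and the rule would still need changing.

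These points limit the size of the claim. They do not answer the core: the rule stands in the protocol, it acts after randomisation, and it has no safeguard.

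**Conclusion.** The point holds as a defect of the analysis rule and should be corrected. Followed as written, section 4.2 takes the primary comparison away from the randomised groups, section 5.2 adds to this, and the conflict with section 9.2.2 leaves the reach of 4.2 unclear. The wording of 4.2 suggests that removed patients also leave the safety analysis; section 9.2.2 says otherwise, so in practice the rule acts on efficacy.

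The size depends on how removal works, which the protocol does not quantify. Power loss is small at 5 to 10% removal (79.8% to 77.9%) and becomes material only at much larger assumed shares. Selectivity common to both arms is a minor matter. The serious risk is selectivity that differs by arm: about 8% or 20% false-superiority risk instead of 5% in the two assumed cases. That such selectivity will occur is not shown; that the rule leaves room for it is.

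**What to change.** Replace the rule in section 4.2 with wording such as: all randomised patients are analysed for efficacy in the arm assigned, whatever their eligibility or deviations, and this is the primary efficacy set. In addition:

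- Keep the present rule only for a per-protocol sensitivity set, limited to major deviations listed in advance and judged without knowledge of arm and outcome.
- State that patients excluded under section 5.2 stay in the primary efficacy set. This concerns the analysis only, not their treatment.
- Reconcile section 4.2 with section 9.2.2, so that the reach of any removal is clear.
- Say how patients who are randomised but not transplanted, or who have DNAemia at transplantation, count towards an endpoint that starts at transplantation.

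The per-protocol set may be reported beside the full set for the secondary aGVHD comparison. This should not be called a non-inferiority test, because section 9.1.1 places that test in the initial design.

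The cost is wording and one extra analysis set, with slight dilution of the dose contrast from non-adherent patients.
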